### Randomization, treatment allocation and allocation concealment

Participating children with dental caries will be categorized into two strata by the number of carious surfaces they have (one to three or more than three tooth surfaces). The children will be then allocated by a stratified randomization method with a block size of 6 into two groups. The allocation sequence will be generated by a technician who will not be involved in the oral examination and patient allocation. A pile of sealed opaque envelopes with the allocation numbers will be prepared. Those envelopes will be held by a dental assistant in the field. The assistant will know the treatment allocation only when they open the envelope.

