### Participants

The eligibility criteria for participating children are as follows: (1) be generally healthy, (2) have written parental consent and (3) have at least one cavitated dentine carious lesion. The exclusion criteria are as follows: (1) children who are uncooperative or who refuse examination and (2) children who have major systemic illnesses or are on long-term medications. A tooth with pulpal exposure or with any signs and symptoms of irreversible pulpitis or a non-vital pulp, such as tooth discoloration, will be excluded.

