### Blinding

Application of the assigned treatment will be carried out after the oral examination. Children’s compliance to fluoride treatment will be recorded and monitored at each treatment visit by an assistant. A double-blinding arrangement will be conducted in this clinical trial. One examiner will perform all the clinical examinations during the study period. The examiner will be blinded to the treatment allocation. The children and their parents also will not be informed of the treatment assignment. The solution and varnish will be applied by an independent operator after the oral examination.

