### Sample size and power calculation

The results of previous clinical trials showed that around 70% of the active dentine caries became arrested after 30 months [18]. The anticipated caries-arresting rates of group B would be 80%. An absolute difference of 10% for the caries-arresting rates between treatment groups is considered to be clinically significant. The sample size calculation is based on the expected proportion of caries that become arrested, with the power of the study set at 90% (*β* = 0.1) and a two-sided 95% confidence interval (*α* = 0.05) as the statistical significance level by using the G*Power Version 3.1.9.2 (Franz Faul, Universität Kiel, Germany). Therefore, at least 820 active carious tooth surfaces need to be included, or 410 in each study group. Based on the results of epidemiological surveys, we anticipate that the mean number of active caries tooth surfaces of 3-year-old children in Hong Kong is approximately three [25]. The intraclass correlation coefficient for dental caries data at the surface level within the individual would be approximately 0.13 [26]. Following the equation for the required sample size in a multilevel study [27], the design effect will be 1.26. Thus, the estimated sample size would be at least 346 children, or 173 per group. The anticipated dropout rate is 15% [24]; thus, 408 children (204 children in each group) will be needed at baseline.

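### A single fixed block size of 6, with envelopes opened by a field assistant who learns each arm, leaves up to a quarter of allocations predictable; undisclosed mixed block sizes would largely remove the certainty

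*Protocol article*

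**What the plan says.** The Protocol article's section on randomization, treatment allocation and allocation concealment forms two strata by number of carious surfaces (one to three, or more than three). It then says: "The children will be then allocated by a stratified randomization method with a block size of 6 into two groups". Only one block size is named. The sequence comes from an independent source: "The allocation sequence will be generated by a technician who will not be involved in the oral examination and patient allocation". Concealment is by envelope: "A pile of sealed opaque envelopes with the allocation numbers will be prepared". A dental assistant holds these in the field, and the section closes with the assurance that "The assistant will know the treatment allocation only when they open the envelope".

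The sample size section gives equal targets: "408 children (204 children in each group) will be needed at baseline". The Screening and recruitment section gives screening to a calibrated examiner. The Blinding section says that one examiner, unaware of allocation, does all the examinations and that an independent operator treats afterwards. The Trial status section reports recruitment in progress from 14 September 2017; the article is dated 4 July 2018.

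**The concern.** Sealed opaque envelopes hide the next assignment only if it cannot be worked out from those already opened. With one fixed block size it sometimes can: once three children in a block have gone to one arm, the rest of that block must go to the other. The assistant who opens the envelopes sees the assignments needed for that deduction. The article does not say that the block size is withheld from field staff.

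What is at stake is selection. If a coming assignment were known, a child could be held back, moved in the order or left out with the arm in mind. Blinding the examiner protects the assessment of arrest but cannot undo an imbalance created at entry.

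**Working it through.** **Inputs.** The block size of 6 and the two strata come from the randomization section. The 1:1 ratio is read from the equal targets of 204 and 204 in the sample size section, which gives 3 + 3 per block. The total is 408 children. The article states no figure for predictability, so there is none to reproduce. Its baseline number does follow from its own inputs: 173 / 0.85 = 203.5, rounded up to 204 per group, or 408.

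**Allocations known with certainty.** A block of 6 with three of each arm has C(6,3) = 20 equally likely orders. Allocations are forced once one arm is used up, so the number forced equals the length of the final run of one arm:

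- final run of 1: 2 × C(4,2) = 12 orders (60%)
- final run of 2: 2 × C(3,2) = 6 orders (30%)
- final run of 3: 2 × C(2,2) = 2 orders (10%)

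Mean = (12 × 1 + 6 × 2 + 2 × 3) / 20 = 30 / 20 = 1.5 per block. The closed form 2m/(m + 1) with m = 3 also gives 1.5. As a share, 1.5 / 6 = 25%. Over 408 / 6 = 68 complete blocks this is 68 × 1.5 = 102 children. Every complete block has at least one forced allocation. Forced places come last, so an unfinished block in a stratum would lower the count slightly.

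**Best guesses.** The rule is to guess the arm with more places left and to toss a coin when the two are level. Over the 20 orders it is right for 4.1 of 6 allocations on average, or 68.3%, against 50% with no information.

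**Effect of mixed block sizes.** Sequences of 204 allocations were simulated 600 times; 204 is one stratum if the strata are equal in size, which is an assumption. The observer knows the set of possible sizes but not the size of the current block, and updates the probabilities after each opening.

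| Block sizes | Known with certainty | Best guess right |
|---|---|---|
| 6 only | 24.9% (exact 25%) | 68.3% |
| 4 and 6 | 5.5% | 69.3% |
| 4, 6 and 8 | 2.3% | 68.0% |

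With 4, 6 and 8, the number known with certainty falls from 102 to about 0.023 × 408 = 9 children. The best-guess rate hardly moves.

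**The case against.** The 25% applies only to someone who knows the block size and keeps an accurate tally in each of two interleaved strata. The article says neither of the assistant, so 102 children is a ceiling and not an expected effect. Publication of the block size came almost ten months into recruitment and could affect only later enrolment.

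The route from prediction to bias is also not described. A blinded examiner screens, eligible children are recruited, and they are allocated after being stratified. The exclusion for "children who are uncooperative or who refuse examination" belongs with the examination, which precedes allocation. The assistant is given no role in eligibility or in assigning the stratum. Both arms receive silver nitrate and a 5% fluoride varnish, so a motive to steer is not obvious. All of this stands, and it limits the point to a risk.

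A reader might go further and infer that field staff choose the order of children, that many are randomised in one session, that the two varnishes look different, or that both strata draw from one stack because the article speaks of a pile. The article says none of these. It gives brand names but not appearance, and the handling of envelope sets is a detail that a journal article commonly leaves to the full protocol.

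The objection does not remove the design choice itself. A single block size is stated, and the person who opens the envelopes necessarily learns the assignments.

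**Conclusion.** The assurance that the assistant knows the arm only at opening is not secured by a fixed block of 6. On average 25% of allocations, at most about 102 of 408, could be known beforehand by a person who knows the block size and tracks assignments by stratum. This rests on 1:1 blocks, inferred from the equal targets, and on complete blocks.

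A reader might infer that concealment has failed or that selection bias has occurred. The documents do not support that. They do not show that anyone holding the envelopes knows the block size, keeps a tally or can influence who enters, and they place screening with a blinded examiner. The point is a moderate predictability risk that is nearly free to reduce. It has no bearing on the sample size.

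**What to change.** For children not yet allocated:

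1. The independent technician generates each stratum's remaining list with randomly varying block sizes, for example 4, 6 and 8, and does not disclose the sizes to field staff.
2. Once eligibility and stratum are recorded, the child's study number is written on the next envelope of that stratum before it is opened.

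The first step lowers certain knowledge from 25% to about 2.3%. It leaves the best-guess rate near 68%, so the second step is needed as well: a child already committed to an envelope cannot be moved on the strength of a guess.

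If allocation is complete, the sponsor can instead report who knew the block size, whether the assistant had any role in enrolment or stratum assignment, and how envelopes were ordered within strata.

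The cost is a new list and relabelled envelopes, with no extra staff, visits or children. The downside is that arm sizes may differ by a few children per stratum. An unfinished block of 8 can leave a difference of up to 4, against up to 3 with a block of 6.

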### Blinding

Application of the assigned treatment will be carried out after the oral examination. Children’s compliance to fluoride treatment will be recorded and monitored at each treatment visit by an assistant. A double-blinding arrangement will be conducted in this clinical trial. One examiner will perform all the clinical examinations during the study period. The examiner will be blinded to the treatment allocation. The children and their parents also will not be informed of the treatment assignment. The solution and varnish will be applied by an independent operator after the oral examination.

### Interventions

A dentist who is not involved in the assessment of the carious lesions will apply the solution and varnish with a micro-brush on the carious lesion according to the assigned treatment group after the oral examination.

Two intervention groups in this study are as follows:Group A: a 25% AgNO_3_ solution (25% silver nitrate, Gordon Labs, Carson, CA, USA) followed by a 5% NaF varnish (Nupro White Varnish, Dentsply, York, PA, USA),Group B: a 25% AgNO_3_ solution (25% silver nitrate, Gordon Labs, Carson, CA, USA) followed by a 5% NaF varnish with fTCP (Clinpro White Varnish, 3 M, St. Paul, MN, USA).

After applying the solution and varnish on the carious lesion(s) for arrest purposes, the assigned 5% NaF varnish (0.25 ml) will be applied on all tooth surfaces of each child to prevent dental caries according to their assigned treatment group. After the treatment, the children will be instructed not to eat or drink for 30 min. The intervention will be provided every 6 months.

An individual report on the child’ s oral health status will be distributed to the parents or guardians with a note asking them to report to the study dentist if there are any adverse effects on the treated tooth and/or the surrounding gum and mucosa after treatment. A referral letter will be provided to seek the appropriate dental treatment if needed. Parents and teachers will be informed that if the treatment has successfully arrested the carious lesions, yellow and soft carious surfaces will become hard and black in color.

### Follow-up evaluation

Follow-up clinical examinations will be conducted semi-annually by the same examiner in kindergartens for 30 months. The same diagnostic criteria, equipment and clinical procedures that were used in the baseline examination will be adopted in the follow-up evaluations. The caries status (dmfs index) and oral health status (VPI) of the children will be recorded. In addition, the status of the carious surfaces included in the study at baseline examination and the presence of visible plaque on those carious surfaces will be assessed. Newly developed carious lesions will be recorded and treated with the assigned treatment intervention. The examiner will also look for related side/adverse effects, including blackening of the treated carious surfaces, discolored teeth, tooth mobility and abscess formation during the follow-up oral examinations. Reasons for tooth loss prior to follow-up will be recorded.

### Outcome measure

Outcome measures will be collected at baseline and semi-annually thereafter for 30 months. The primary outcome measure of this study is the proportion of soft (active) carious surfaces that become hardened (arrested). Lesion activity will be assessed based on visual and tactile sensation. A lesion will be recorded as active if softness is detected upon gentle probing, and it will be classified as arrested caries if the lesion is hard [19, 24].

The secondary outcome measure is the caries increment or the change in the dmfs score over time, which will be measured by a calibrated dental examiner who is masked to the group assignment. Visual and tactile inspection without x-rays will be adopted.

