### Objective

The objective of this randomized, double-blind controlled trial is to compare the caries-arresting effectiveness of a 5% NaF varnish with fTCP and that of a 5% NaF without fTCP when applied semi-annually following the application of a 25% AgNO_3_ solution in preschool children over 30 months. The secondary objective is to compare the effectiveness of a 5% NaF varnish with fTCP and that of a 5% NaF without fTCP in preventing dental caries in preschool children over 30 months.

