### Clinical examination

Clinical examination of the children will be performed mainly through a careful visual inspection with the aid of a World Health Organization CPI probe (405/WHO probe, Otto Leibinger, Mühlheim, Germany) and a disposable dental mirror with an attached light-emitting diode for intra-oral illumination (MirrorLite, Kudos Crown Limited, Hong Kong Special Administrative Region of the People’s Republic of China). Tooth status (decayed, missing and filled tooth surfaces (dmfs) scores), tooth mobility and tooth discoloration will be recorded. Caries will be diagnosed at the cavitation level. The visual-tactile assessment will be adopted to assess the status of carious lesions. They will be gently explored with a CPI probe in the centre of the lesion. Great care will be taken to avoid damaging the tooth. For the posterior teeth, all five surfaces (buccal, lingual, mesial, distal and occlusal) will be assessed, while four surfaces (buccal, lingual, mesial and distal) of the anterior teeth will be examined.

The oral hygiene status will be measured using the Visible Plaque Index (VPI). The buccal and lingual surfaces of six index teeth (55, 51, 63, 71, 75 and 83) will be examined. The presence or absence of visible plaque on the carious surface will also be recorded. No dental radiograph will be taken because this study will be conducted in a school-based setting.

A trained dentist will perform the examinations (baseline and follow-ups) throughout the 30-month study. The intra-examiner agreement on the plaque and caries assessment will be performed in 10% of the children at each stage of the study.

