### Surface-level analysis

Because more than one carious lesion may be included from one child, these lesions will possibly be correlated or clustered. Therefore, an adjustment of the clustering effect will be required. Multilevel logistic regression analysis will be adopted to assess the relative effectiveness of a 25% AgNO_3_ and a 5% NaF varnish with or without fTCP in arresting dentine caries. A two-level model will be used: level 1, tooth surface level, and level 2, subject level. Multilevel logistic regression models with a clustering effect adjustment will be performed to analyze the effect of independent variables on the caries-arresting outcomes at the 12-, 18- and 30-month follow-ups. Besides treatment group assignment, other potential variables, such as demographic characteristics (sex and age), oral hygiene status, oral-health-related behaviors, level of parental education, family income, caries condition (baseline dmfs scores, tooth position, lesion site and presence of plaque on lesion), also will be included in the model as covariates.

The secondary outcome (preventive effect) is the mean of caries increment at the 6-, 12-, 18-, 24- and 30-month examinations. A paired *t* test will be performed to assess the difference in the caries increment between the two groups at all follow-up examinations. Multilevel generalized linear models will be adopted to assess the effect of independent variables on the caries increment between two groups at 12, 18 and 30 months.

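### The preventive outcome is equated with net change in whole-mouth dmfs, which still counts new caries but does not isolate prevention from the fate of teeth carious at baseline

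*Protocol article*

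**What the plan says.** Under Objective, the protocol article sets as its secondary aim a comparison of the two varnishes "in preventing dental caries in preschool children over 30 months". Under Outcome measure it defines the matching endpoint: "The secondary outcome measure is the caries increment or the change in the dmfs score over time". Surface-level analysis repeats it under a stronger label: "The secondary outcome (preventive effect) is the mean of caries increment at the 6-, 12-, 18-, 24- and 30-month examinations".

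The components of the index are given under Clinical examination: "Tooth status (decayed, missing and filled tooth surfaces (dmfs) scores), tooth mobility and tooth discoloration will be recorded". The same section fixes the number of surfaces per tooth: "For the posterior teeth, all five surfaces (buccal, lingual, mesial, distal and occlusal) will be assessed", and "four surfaces (buccal, lingual, mesial and distal) of the anterior teeth will be examined". Under Participants, each child must "have at least one cavitated dentine carious lesion", so baseline dmfs is at least 1 in everyone.

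Follow-up evaluation plans two useful data items. New lesions are recorded, and "Reasons for tooth loss prior to follow-up will be recorded". Neither Outcome measure nor Surface-level analysis says that these items enter the secondary outcome.

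**The concern.** A caries increment can mean new disease on surfaces that were sound. It can also mean the difference between two whole-mouth totals. The article joins the two with a simple *or*, and the second does not isolate prevention in this population.

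The total includes the very teeth whose lesions the primary outcome follows. If such a tooth is extracted or fully covered, its remaining sound surfaces can enter the missing or filled count although no new surface has decayed. If it is shed naturally and no longer scored, its decayed surfaces leave the count and the increment falls.

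The first route has a direction under the trial's own hypothesis. If fTCP improves arrest, and lesions that fail to arrest lead to loss or full coverage more often than arrested ones, group B would show a smaller dmfs change even if fTCP prevented nothing. The Discussion says that preventive information is lacking and offers the trial as a source of it, so the arrest and preventive effects should be separable in the results.

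**Working it through.** **The plan's own figures.** No effect size, SD or sample size is given for the dmfs outcome, so there is nothing to reproduce there. The number per group used below comes from Sample size and power calculation:

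- At 410 surfaces per group, Fisher's exact test of 70% v 80% has power 0.900, which matches the stated 90%.
- Design effect: 1 + (3 − 1) × 0.13 = 1.26.
- Children per group: 410 × 1.26 / 3 = 172.2, rounded up to 173, or 346 in total.
- With 15% dropout: 346 / 0.85 = 407.1, rounded up to 408.

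These agree with the article and are not touched by this point.

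**Step 1: what one tooth can do to the score.** A posterior tooth has 5 surfaces and an anterior tooth 4 (Clinical examination). For a tooth with k carious surfaces at baseline:

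- Extracted and scored missing, or fully covered and scored filled: change = 5 − k (posterior) or 4 − k (anterior). With k = 1 this is +4 or +3.
- Shed naturally and no longer scored: change = −k.
- If shed teeth were instead scored as missing, a sound tooth would add +5 or +4 on shedding.

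The article does not say which convention applies to shed teeth.

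**Step 2: how much of an arrest effect could leak.** From the sample size section: 3 active surfaces per child, with arrest of 70% v 80%.

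- Non-arrested surfaces per child: 3 × 0.30 = 0.9 and 3 × 0.20 = 0.6, a difference of 0.3.
- Spurious difference in mean increment = 0.3 × q × s, where q is the proportion of teeth with non-arrested lesions that are lost and s is the surfaces added (3 or 4).

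Assumptions, none from the article: q runs from 5% to 30%; teeth with arrested lesions are not lost; each lesion sits alone on its tooth; the true preventive effect is zero.

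- Low end: 0.3 × 0.05 × 3 = 0.045 surfaces per child.
- High end: 0.3 × 0.30 × 4 = 0.36 surfaces per child.

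**Step 3: would a test notice it?** For a two-sided 5% comparison of means with 173 per group and an assumed SD of 2 to 5, let z = d / (SD × √(2/173)), where d is the spurious difference. The rejection rate is Φ(z − 1.96) + Φ(−z − 1.96).

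| q (assumed) | d, anterior to posterior | False rejection, SD 5 down to 2 |
|---|---|---|
| 5% | 0.045 to 0.06 | 5% to 6% |
| 10% | 0.09 to 0.12 | 5% to 9% |
| 20% | 0.18 to 0.24 | 6% to 20% |
| 30% | 0.27 to 0.36 | 8% to 39% |

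Example, top of the last row: 0.36 / (2 × √(2/173)) = 0.36 / 0.215 = 1.67, which gives 0.388.

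**Step 4: shedding.** Entry at 3 to 4 years plus 30 months gives an age of at least 5.5 years at the end, and the Discussion says that all children will then be eligible for primary school. That incisors begin to shed in this window is an assumption. Shedding driven by age should be similar in randomized groups, so it mainly adds variance and negative increments at late visits.

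**The case against.** The strongest reply is that surface-coding rules for extracted, crowned and shed teeth commonly sit in the full protocol or analysis plan, neither of which is shown. The article also names caries increment, and it plans to record new lesions and reasons for tooth loss, so the data needed for a clean derivation will exist. This stands as far as the missing scoring detail goes, and that detail alone would be no finding. It does not remove the point, because what the article does state treats net dmfs change as interchangeable with the increment and labels the result preventive.

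Three stronger readings are tempting, and the documents support none of them:

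- *The outcome does not measure prevention at all.* The assigned varnish goes on all tooth surfaces, and each newly cavitated surface raises dmfs. The measure is contaminated, not void.
- *Better arrest by itself lowers the increment.* If an arrested cavity is still scored as decayed (the article does not say), arrest alone leaves dmfs unchanged. The leak needs tooth loss, a restoration on further surfaces, or spread of the lesion.
- *Shedding biases the comparison.* Randomization should balance it.

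The size is also fairly disputed. Ethical consideration reports that most participants in earlier trials did not go to other dental personnel, which suggests few extractions or crowns, although Interventions does provide for referral letters. Lesions that share a tooth would mean fewer teeth lost and fewer sound surfaces recoded per tooth, so the Step 2 figures lean high for a given q.

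**Conclusion.** The point holds in a limited form. The article equates caries increment with net dmfs change and calls it the preventive effect, in children who all have carious teeth at entry. Net change includes new lesions but does not isolate prevention, and part of an arrest effect could be reported as prevention.

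The size cannot be found from the article. The range of about 0.05 to 0.36 surfaces per child rests on the assumed loss of 5% to 30% of teeth with non-arrested lesions and on the planned 10-point arrest difference being real. At the low end the effect is negligible. False rejection rises well above 5% only with frequent loss and a small SD.

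This is a secondary outcome. The primary outcome, the sample size and the conduct of the trial are unaffected. The change is worth making because it is cheap and would settle, before results are seen, which of two derivations carries the preventive claim.

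**What to change.** Under Outcome measure and Surface-level analysis, define the preventive outcome as the number of surfaces sound at baseline that become decayed, are filled because of caries, or are lost because the tooth, itself sound at baseline, was extracted for caries.

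Use the recorded reasons for tooth loss so that two things are not scored as new caries: naturally shed teeth, and the remaining sound surfaces of baseline-carious teeth that are extracted or fully covered.

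Those surfaces can no longer develop caries. Ignoring this would favour the group that loses more teeth, so account for it, for example with the number of surfaces at risk as an offset or with a sensitivity analysis. Keep net dmfs change as a supportive measure.

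One limit remains. Spread of a treated lesion to a neighbouring sound surface counts as new caries under either definition.

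The cost is slightly more derivation work on data already planned, and less direct comparability with trials that report net dmfs.
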